### Secondary Hypotheses

Compared to women who receive usual care alone, women randomized to the decision aid arm will be **a)** less likely to select sterilization and more likely to select an alternative method, and **b)** will be more satisfied with their decision at 3-month postpartum follow-up.

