Medicaid policy currently requires that people requesting a federally-funded sterilization complete a standardized consent form at least 30 days prior to the surgery. This policy was originally instituted in the 1970s to protect vulnerable women from coercive sterilization practices by attempting to ensure informed and voluntary consent. However, there is mounting evidence that the consent form is not capable of ensuring patient comprehension, as the reading level is much higher than the average literacy level of the people it intends to serve and misunderstandings about the procedure are common after reviewing the form. Furthermore, for many women requesting postpartum sterilization, the mandatory 30-day waiting period and the necessity of successful transfer of the consent form to the delivery suite have created logistical obstacles that preclude them from getting a desired procedure. Thus, there is growing consensus that the policy is not only incapable of ensuring informed consent, but also impedes access to desired sterilization for many low income women. As the relatively recent alleged coercive sterilizations among female California inmates attest, protection for vulnerable women is still needed. However, given the high rates of unwanted pregnancy among women who request but do not undergo sterilization, reducing barriers to desired sterilization is also critical. The lack of a process that meets these two goals – informed consent and timely access – is a critical impediment to progress toward reproductive health equity for low-income women.

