### Time 3 Assessment

The final Time 3 (T3) assessment will also be conducted via telephone 3 months postpartum to determine which method, if any, women are actually using and satisfaction with their decision. T3 follow-up contact will not exceed 4 weeks from the date of the first contact attempt and follows the same standards for maximum attempts of contact as T2. As the 3-month follow-up is likely too proximal to experience regret for sterilization decisions, we will focus on other widely-used constructs (decisional conflict and satisfaction with decision) that are strongly correlated with decisional regret.

For those participants whose pregnancy ends before T2 due to miscarriage, termination, or stillbirth, the research team will only proceed with T3 if the participant wishes to continue with their participation. If the participant agrees to be contacted for a T3 interview, T3 follow-up contact will begin at least 3 months after the date the pregnancy ended.

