## Sample Size Calculation

We based our sample size on the standardized mean differences (Cohen’s d) for the co-primary outcomes of knowledge (0.46) and decisional conflict (0.36) reported in the 2014 Cochrane review of decision aid RCTs. Assuming two-sided alpha levels of 0.025 (for each co-primary outcome) and 15% attrition, 175 women per arm afforded us 80% power to detect these differences.

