| Subsequent Pregnancy Since Delivery                            | Assessed by participant-reported survey responses to a Yes/No item about whether a pregnancy has occurred since delivery.                                                                                                                                                                                                                                                                                                                                                                   | T3: 3 months postpartum                                       | Dichotomous (yes/no)  | Dichotomous (yes/no)                                                                                                                                                                                                                                                                                                                                                                                           |
| Participant Satisfaction with Sterilization Counseling         | Participant responses to an 8-item patient-provider communication scale created by the PI to assess participant satisfaction with the sterilization counseling experience. Response options range from 1 ("Strongly Disagree") to 5 ("Strongly Agree"). Items will be examined individually. In addition, a summary score will be created with items 2,3,6 reverse coded such that the range will be 8-40 with a higher score reflecting greater satisfaction with sterilization counseling | T3: 3 months postpartum                                       | Continuous (8-40)     | Continuous (8-40)                                                                                                                                                                                                                                                                                                                                                                                              |

420  
421  
422

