### Exploratory Hypotheses

For the following exploratory hypotheses, regression will be used to test intervention effects controlling for study site. The beta coefficient and corresponding 97.5% confidence interval will be used to assess the effect of the intervention.

- **Pre- and Post-Dobbs SCOTUS Decision Exploratory Analyses:** regression analyses are adjusted for study site  
\*\*note state interaction effects below\*\*
  - Date for the *Dobbs* decision can be categorized in 3 ways:
    - Dichotomized as before June 24, 2022 and June 24, 2022 or later (the verdict)
    - Dichotomized as before May 1, 2022 and May 1, 2022 or later (the leak)
    - Categorical: before May 1; May 1- June 23; June 23 or later (would measure effect of the leaked news and then effect of the full impact)
  - How did the *Dobbs* SCOTUS decision impact recruitment?
    - Recruitment changes pre- and post-Dobbs
      - More interest in joining study
      - Differences in recruitment across gravida and parity
  - How has it affected our outcomes of interest?
    - The desire for sterilization at baseline
    - Decisional conflict about contraceptive method selection at T1 predicted by date
    - Ease in contraceptive decision making at T1 and T2 predicted by date
    - Certainty about sterilization decision at T1 and T2 predicted by date
    - Contraceptive method selected at T1 and T2 predicted by date
    - Contraceptive method used at T3 predicted by date

- **\*\*Interaction effect between date and state on all outcomes (for every outcome)\*\***

- **Additional Sensitivity Analyses for Primary and Secondary Outcomes**

- We will run additional sensitivity analyses to test robustness of the intervention effects after adjusting for any significant differences in baseline characteristics (to be identified during analysis) between the intervention and control group that are also associated with the outcomes of interest:
  - 1) sterilization knowledge at T1
  - 2) decisional conflict at T1
  - 3) contraceptive method selected at T1
  - 4) satisfaction with decision-making at T3
- We will run additional sensitivity analyses to test robustness of the intervention effects after adjusting for differences in:
  - T3 Outcomes (satisfaction with decision-making at T3):

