- **Ease in Contraceptive Decision Making at Time 2:** Compared to women who receive usual care alone, women randomized to the decision aid arm will report greater ease in contraceptive decision making at Time 2
- **Certainty about Tubal Sterilization Decision at Time 1:** Compared to women who receive usual care alone, women randomized to the decision aid arm will report a) greater certainty about tubal sterilization decision at Time 1 and b) greater certainty in general, regardless of whether that’s for or against tubal sterilization
  - Multinomial regression (certain about not getting it vs. uncertain vs. certain about getting it) will be used to test intervention effects controlling for study site
  - Linear regression will be used (5-10, uncertain to certain) to test intervention effects controlling for study site
  - Logistic regression will be used (uncertain vs certain) to test intervention effects controlling for study site
- **Certainty about Tubal Sterilization Decision at Time 2:** Compared to women who receive usual care alone, women randomized to the decision aid arm will report a) greater certainty about tubal sterilization decision at Time 2 and b) greater certainty in general, regardless of whether that’s for or against tubal sterilization
  - Multinomial regression (certain about not getting it vs. uncertain vs. certain about getting it) will be used to test intervention effects controlling for study site
  - Linear regression will be used (5-10, uncertain to certain) to test intervention effects controlling for study site
  - Logistic regression will be used (uncertain vs certain) to test intervention effects controlling for study site
- **Participant Confidence in Contraceptive Method Selection at Time 3:** Compared to women who receive usual care alone, women randomized to the decision aid arm will report greater confidence that their current contraceptive method(s) is “right for them” at Time 3
- **Subsequent Pregnancies Since Delivery at Time 3:** Compared to women who receive usual care alone, women randomized to the decision aid arm will report lower likelihood of having a subsequent pregnancy at Time 3

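### Subsequent pregnancy at 3 months is assessed only by a site-adjusted regression coefficient, which has no finite value if an arm has no events; counts and a risk difference should replace it (minor point)

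*Combined protocol and SAP*

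**What the plan says.** The table of Exploratory Outcome Measures defines subsequent pregnancy as "Assessed by participant-reported survey responses to a Yes/No item about whether a pregnancy has occurred since delivery". It is collected at T3 only, by telephone, 3 months postpartum. It counts any pregnancy and does not ask whether the pregnancy was wanted.

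The hypothesis, under Exploratory Hypotheses, is that "women randomized to the decision aid arm will report lower likelihood of having a subsequent pregnancy at Time 3". No method is given for this outcome alone. The rule at the head of that section applies: "regression will be used to test intervention effects controlling for study site. The beta coefficient and corresponding 97.5% confidence interval will be used". No other measure of effect is named there. The section does not say logistic regression for this item; that is inferred from the yes/no outcome and from the mention of linear or logistic regression under Primary and Secondary Hypotheses.

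Descriptive and Baseline Statistics commits to means or proportions with confidence intervals for the primary and secondary outcomes. Subsequent pregnancy is exploratory, so that commitment does not reach it.

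On timing, Time 3 Assessment says "As the 3-month follow-up is likely too proximal to experience regret for sterilization decisions" and substitutes other constructs for regret. It makes no comparable remark about pregnancy.

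**The concern.** A regression coefficient is a poor sole summary of an outcome that may have very few events. If no woman in one arm reports a pregnancy, the maximum likelihood estimate of the arm effect is infinite and its Wald interval is meaningless. Followed literally, the plan would then leave nothing to report, because no counts, percentages or absolute difference are promised. If both arms have some events, the coefficient exists but may be compatible with a large change in either direction.

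The item matters somewhat more than its place in a long exploratory list suggests. The aid is expected to make women "less likely to select sterilization and more likely to select an alternative method", and the Research Background argues for access to sterilization "given the high rates of unwanted pregnancy among women who request but do not undergo sterilization". Readers of the results will look for the pregnancy figures. A directional benefit hypothesis attached to an estimate this imprecise, with no note on timing, makes those figures easy to misread.

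**Working it through.** **The plan's own figure.** Sample Size Calculation uses "two-sided alpha levels of 0.025 (for each co-primary outcome) and 15% attrition", with standardized differences of 0.46 and 0.36. The smaller one drives the size: 2 × (2.241 + 0.842)² / 0.36² ≈ 147 per arm, and 147 / 0.85 ≈ 173 (174 with the t distribution), against 175 stated. The figure reproduces, but it sizes only the two T1 scores. The plan states no event rate, power or precision for pregnancy.

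**Inputs.**
- Women per arm at T3: 175 × 0.85 = 148.75, taken as 149. This applies the stated attrition to T3.
- Interval level: 97.5%, so z = 2.241.
- Pregnancy rate p by 3 months postpartum: not in the documents. Assumed 0.5% to 3%, equal in both arms.

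**Step 1: chance of an empty arm.** One arm has no events with probability q = (1 − p)^149. At least one arm is empty with probability 2q − q²; both are empty with probability q². At p = 1%: q = 0.224, so 2q − q² = 0.397 and q² = 0.050.

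**Step 2: width when the counts equal their expectation.** For a true odds ratio of 1, the 97.5% interval is exp(± 2.241 × √(2/(149p) + 2/(149(1 − p)))). At p = 1% the root is √(1.342 + 0.014) = 1.164, giving exp(± 2.61), or 0.07 to 13.6. Site is ignored here.

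| Assumed rate | Expected events per arm | At least one arm empty | Both arms empty | 97.5% interval for the odds ratio |
|---|---|---|---|---|
| 0.5% | 0.7 | 72% | 22% | 0.03 to 40 |
| 1% | 1.5 | 40% | 5% | 0.07 to 13.6 |
| 2% | 3.0 | 10% | 0.2% | 0.16 to 6.4 |
| 3% | 4.5 | 2% | under 0.1% | 0.22 to 4.6 |

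If the aid arm's true rate were double the control rate shown, the chance of an empty arm would be 59%, 26%, 5% and 1%.

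**Step 3: does an empty site matter?** With three equal sites (assumed, 298/3 women each), the chance that at least one site has no events is 1 − (1 − (1 − p)^(298/3))³, or 94%, 75%, 35% and 14%. This makes that site's own term infinite but leaves the arm term alone. For example, with 50 women per arm per site and events of 1 v 2, 1 v 1 and 0 v 0, the arm coefficient is 0.416 with standard error 0.924, the same as when the empty site is dropped. Only the empty-arm column bears on the treatment estimate.

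**Step 4: what an absolute measure gives.** With 3 v 6 events among 149 per arm, the odds ratio is 2.0 (97.5% interval 0.41 to 10.2) and the risk difference is 2.0 percentage points (−3.1 to +7.6, Newcombe). With no events in either arm, the odds ratio does not exist, yet the risk difference interval is still about ±3.3 points.

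**The case against.** The case against is substantial, and most of it stands.

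- The event rate is assumed. An empty arm is likely only at about 1% or below and is uncommon from 2% upward. What holds across the whole range is the imprecision.
- Low power for an exploratory outcome with no power claim is not a defect, and no analysis method adds information.
- A reader might infer that the planned model breaks down whenever a site has no events, which would make failure look far more frequent. Step 3 shows that the arm estimate survives an empty site.
- A reader might infer that the benefit wording would hide a rise in pregnancies. Only the hypothesis is directional. The stated interval is not one-sided, so a rise would show in the estimate and the upper limit, and no rule in the plan equates a non-significant result with no effect.
- A reader might infer that the trial is mishandling its measure of unwanted pregnancy. The item counts any pregnancy. The background statement concerns women who asked for sterilization and did not get it, whereas the aid is expected to lead women to choose another method, and the Research Background says that some reversible methods match sterilization in efficacy.
- The rule says only regression, so a penalised or exact model may already be permitted.

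The last point does not remove the gap. Nothing directs the analyst to such a model, no absolute measure is planned, and a directional hypothesis remains on data that cannot speak to it with useful precision.

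**Conclusion.** The point holds as a minor one. As written, the sole planned summary of subsequent pregnancy has no finite arm estimate if an arm has no events, with probability about 72%, 40%, 10% and 2% at assumed rates of 0.5%, 1%, 2% and 3%. Even at 3%, with equal rates and expected counts, the odds ratio interval is about 0.22 to 4.6.

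These figures rest on an event rate that the documents do not give, on 15% attrition applying to T3, on equal rates in the arms, and on reading regression as logistic. Greater loss by T3 would make them worse.

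The documents do not support a claim that the plan conceals harm, or that the treatment estimate is usually lost whatever the rate. No primary or secondary conclusion depends on this item.

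**What to change.** Under Exploratory Hypotheses, exempt subsequent pregnancy from the general coefficient rule and replace the directional hypothesis with the following:

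- Report number and percent by arm among T3 respondents, with an exact confidence interval for the risk difference.
- If an odds ratio is wanted, use Firth-penalised logistic regression adjusted for site, or exact conditional logistic regression stratified by site. With one empty arm the exact conditional model gives only one finite limit, and with no events at all it gives nothing, so the counts and risk difference should come first.
- State that T3 pregnancy data are descriptive and will not be used to conclude that the aid lowers, or does not raise, pregnancy. A sentence beside the existing remark on regret in Time 3 Assessment would do.

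The cost is a few lines of SAP wording, slightly more analysis work, and the loss of one exploratory directional test. No new data, visits or staff are needed.

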## **Exploratory Analyses in Specific Subset(s) of the Sample**

*\*Note: these analyses on specific subsets of the sample no longer rely on the randomization process. Each of the analyses below will need to assess for potential confounding factors and control for those factors in addition to study site:*

### 1) Among People who Wanted Sterilization at Time 2:

- What Contraceptive Method(s) are Used at Time 3: binary logistic regression will be used to test intervention effects on odds of sterilization vs all other methods controlling for study site and other potential confounders
  - We specifically hypothesize that intervention group members will be less likely to report using sterilization as compared to the control group

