## Research Background

Female surgical sterilization is the most commonly used contraceptive method in the US among women 15-49 years, and historically has been disproportionately used by low-income women and women of color. Whether the higher use of sterilization in these populations reflects inappropriate overutilization is unclear. On one hand, low-income and racial minority women frequently misunderstand the permanent nature of sterilization; are often unaware of reversible contraceptive alternatives with similar efficacy, convenience, and safety profiles as sterilization; and commonly experience post-sterilization regret – suggesting suboptimal decision making. On the other hand, there is evidence of substantial unmet demand for sterilization among low-income women, due to unique access barriers posed by Medicaid sterilization regulations, putting them at high risk for undesired pregnancy and the adverse health and social consequences associated with unwanted pregnancies and births.

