| The consent form was not completed on time or in its entirety                                             | For people who reported at T2 wanting sterilization as their method but did not undergo sterilization                                                                                                                                            | T3 | Dichotomous (yes/no) | Dichotomous (yes/no)                             |
| The operating room was not available                                                                      | For people who reported at T2 wanting sterilization as their method but did not undergo sterilization                                                                                                                                            | T3 | Dichotomous (yes/no) | Dichotomous (yes/no)                             |
| The wait between your delivery and getting the procedure was too long                                     | For people who reported at T2 wanting sterilization as their method but did not undergo sterilization                                                                                                                                            | T3 | Dichotomous (yes/no) | Dichotomous (yes/no)                             |
| You decided you wanted a reversible method of contraception                                               | For people who reported at T2 wanting sterilization as their method but did not                                                                                                                                                                  | T3 | Dichotomous (yes/no) | Dichotomous (yes/no)                             |

|                                               |                                                                                                              |    |                      |                                                  |
|-----------------------------------------------|--------------------------------------------------------------------------------------------------------------|----|----------------------|--------------------------------------------------|
|                                               | undergo sterilization                                                                                        |    |                      |                                                  |

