### 2) Among People who Wanted Sterilization at Time 2 but Did Not have Sterilization at T3:

- What are their Reasons for Contraceptive Method(s) Mismatch: a series of logistic regressions will be used to test intervention effects on *reasons for mismatch* controlling for study site and potential confounders
  - We specifically hypothesize that intervention group members will be less likely to report logistical barriers.
    - Logistical barriers are defined as any of the following reasons: Financial concerns, Method was unavailable/too difficult to obtain, Method was too difficult to use

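### Among women who want sterilization at T2, the plan predicts fewer sterilizations in the aid arm without a rationale, and its binary outcome pools a change of mind with failure to obtain the procedure

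*Combined protocol and SAP*

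**What the plan says.** The section on exploratory analyses in specific subsets has three items. Item 1 is headed "Among People who Wanted Sterilization at Time 2". Its method is that "binary logistic regression will be used to test intervention effects on odds of sterilization vs all other methods", adjusted for site and possible confounders, and it adds: "We specifically hypothesize that intervention group members will be less likely to report using sterilization as compared to the control group". No rationale follows.

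Item 2 keeps only those women in item 1 who were not sterilized by T3 and fits a series of logistic regressions by arm on their reasons. It states: "We specifically hypothesize that intervention group members will be less likely to report logistical barriers". The section opens with the caution that "these analyses on specific subsets of the sample no longer rely on the randomization process".

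The reasons are separate yes/no items in the Exploratory Outcome Measures table. For women who wanted sterilization at T2, they include an incomplete or late consent form, an unavailable operating room, too long a wait after delivery, financial concerns, medical concerns, worry about anesthesia, concern about recovery, and "You decided you wanted a reversible method of contraception". A free-text field for other reasons is also provided.

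The Research Background says that "there is evidence of substantial unmet demand for sterilization among low-income women" and that "reducing barriers to desired sterilization is also critical". The Study Objectives and Hypotheses cover knowledge, decisional conflict, method selected and satisfaction. Obtaining a wanted sterilization is not among them.

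**The concern.** For all randomized women, the secondary hypothesis that the aid leads fewer to select sterilization is coherent, because the choice is still open at T1. Item 1 carries the same direction into a group where the choice has been stated. According to the Time 2 Assessment section, T2 comes after the point at which the Medicaid consent form is usually signed. By then these women have had the aid or usual care, and they still want the procedure.

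Not being sterilized by T3 then means one of two quite different things: the woman changed her mind, or she wanted the procedure and did not get it. The binary outcome does not separate them. At stake is the reading of the result. A lower odds ratio in the aid arm would match the stated prediction even if it came wholly from women who were blocked. A higher odds ratio, which could reflect better access, would run against it.

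**Working it through.** **Inputs.** The documents give no size, receipt rate or expected effect for this subset, so there is no planned figure to reproduce. The 175 per arm in the Sample Size Calculation was derived for the co-primary outcomes. All counts and rates below are assumptions for illustration.

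**1. What the predicted direction means.** Within the subset, non-receipt = 1 − receipt. With control receipt p and odds ratio OR, odds in the aid arm = OR × p/(1 − p), and receipt = odds/(1 + odds). For an assumed OR of 0.7:

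| Control receipt (assumed) | Aid-arm receipt | Non-receipt, control | Non-receipt, aid |
|---|---|---|---|
| 50% | 41% | 50% | 59% |
| 60% | 51% | 40% | 49% |
| 70% | 62% | 30% | 38% |

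Any OR below 1 therefore means more unfulfilled T2 preferences in the aid arm. With the opposite direction (OR 1.43), non-receipt in the aid arm falls to 41%, 32% and 23%.

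**2. What the binary outcome hides.** Assume 75 such women per arm, with 45 sterilized in the control arm (60%) and 38 in the aid arm (51%).

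- OR = (38/37)/(45/30) = 1.027/1.5 = 0.68.
- Non-receipt is 37 against 30, a difference of 7 women. The OR is 0.68 if all 7 chose a reversible method, and 0.68 if all 7 were blocked.

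**3. Whether item 2 fills the gap.** Item 2 conditions on non-receipt. Continue the same counts and assume that an access barrier is reported by 15 of 30 unsterilized control women and 18 of 37 unsterilized aid-arm women.

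- Item 2 compares (18/19)/(15/15) = 0.95, in the direction of fewer barriers with the aid.
- With all T2-wanters as denominator, the blocked proportions are 18/75 = 24% and 15/75 = 20%, so more women were blocked in the aid arm.

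The share of reasons among unsterilized women can fall while the proportion of all wanters who were blocked rises.

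**4. Item 2's barrier definition against the item list.** Item 2 defines a logistical barrier by three reasons. In the Exploratory Outcome Measures table, financial concerns is listed for women who wanted sterilization. The other two (method unavailable or hard to obtain; method hard to use) are listed only for women who wanted some other method. The consent form, operating room and wait items, which are listed for women who wanted sterilization, are left out.

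**5. The direction against the rest of the plan.** The Exploratory Hypotheses section expects greater certainty in the aid arm at T2, whether for or against sterilization. The Assessment of Potential Risks and Benefits describes the tool as supporting decisions that fit the woman's values. Neither gives a reason to expect more late reversals among aid-arm women who want the procedure at T2.

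**The case against.** The strongest reply has five parts.

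- **Access is background, not an objective.** A reader might infer that the trial sets out to reduce unmet demand and would count its opposite as success. The documents do not support that. The objectives and hypotheses do not include fulfilment, and the two goals in the Research Background describe a process that is lacking. This stands.
- **No success criterion attaches to the analysis.** It is exploratory, the plan itself says that randomization no longer protects it, and no one-sided test is specified. If the 97.5% interval in the Exploratory Hypotheses section applies here, the assumed example gives SE(log OR) = √(1/38 + 1/37 + 1/45 + 1/30) = 0.33 and an unadjusted interval of about 0.33 to 1.43 (p about 0.25), which does not support the prediction. An odds ratio above 1 would be equally visible. This stands: the stated direction changes no computation, only the interpretation.
- **The plan already analyses reasons by arm.** It would be wrong to say that the plan makes no attempt to separate choice from access. Item 2 does so, and its regressions are not confined to the composite. But it is restricted to unsterilized women, so it cannot give the proportion of wanters who were blocked. The separate calculation of women who signed the Medicaid consent without being sterilized uses signers as its denominator, not T2-wanters.
- **The two hypotheses do not contradict each other.** Fewer sterilizations and fewer logistical reasons among the unsterilized can both hold if non-receipt in the aid arm is more often by choice. This stands, but the plan does not say that this is its expectation.
- **Not every reason other than choosing a reversible method is an access failure.** Worry about anesthesia or recovery can be the woman's own decision, and one woman can report several reasons. This stands and shapes the fix.

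**Conclusion.** The point holds as a fault of interpretation in one exploratory analysis. The direction is unexplained, and it fits poorly with the access need in the Research Background and with the greater T2 certainty expected elsewhere in the plan. A result in that direction necessarily means more unfulfilled T2 preferences in the aid arm. For an assumed odds ratio of 0.7, that is about 8 to 9 percentage points more non-receipt when control receipt is 50% to 70%. Whether those women changed their minds or were blocked cannot be read from item 1, and item 2 gives only shares among the unsterilized.

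The sizes rest on assumed counts and rates, because the documents give none. The logical points (non-receipt is the complement of receipt, and item 2 has a different denominator) rest on no assumption. No primary or secondary result is affected. The stronger inference, that the plan treats unmet demand as a success of the trial, is not supported.

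**What to change.** In item 1, make the hypothesis non-directional, or state why fewer sterilizations are expected among women who still want the procedure at T2. Keep the logistic model if wished, and add a table by arm with all T2-wanters as denominator, showing how many lack a T3 interview:

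1. sterilization obtained;
2. not obtained, with an access barrier reported (for example the consent form, operating room, wait and financial items);
3. not obtained because of changed preference or another reason, with the individual items listed beneath.

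Assign each reason to level 2 or 3 before the analysis, and give a precedence rule for women who report several. State that the odds ratio will be read with this split, and that a lower value will not be described as favourable unless it reflects changed preference and not access failure. In item 2, align the definition of logistical barriers with the reasons listed for women who wanted sterilization.

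The cost is SAP wording and one variable derived from items already collected. The downside is smaller cells in a subset that is already exploratory, so the split should be reported mainly as proportions with intervals.
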